## Abstract

**Background:**

Aggression and violence are prevalent in forensic psychiatric inpatient care. These behaviors significantly impact treatment outcomes, create challenging work environments for staff, and strain relationships between patients and caregivers. Managing such behaviors poses a formidable challenge that necessitates innovative approaches and evidence-based interventions. The Therapeutic Meeting with Aggression (TERMA) model is a staff training program designed to equip staff with strategies to de-escalate patient aggression, thus reducing violence and increasing patients’ and staffs’ perceived safety.

**Objective:**

The aim of this project is to evaluate the violence prevention model TERMA regarding perceived safety by patients and staff and adverse events within forensic psychiatric inpatient care. In addition, the project will investigate whether the organizational culture affects the implementation of the TERMA model.

**Methods:**

The project includes an observational study with a before and after design. Implementation of the TERMA model consists of an 8-seminar staff training program. Data sources include questionnaires, medical records, and registries. Quantitative data will be analyzed using descriptive and comparative statistics. To analyze changes between measurements, dependent sample 2-tailed *t* tests will be used for normally distributed data, and the Wilcoxon signed-rank test will be applied when normality is not met. The project will also include qualitative interview studies, which are planned to be analyzed using qualitative inductive content analysis.

**Results:**

Participant enrollment began in July 2023 and was concluded by the end of 2024. Data collection and analysis of quantitative data are expected to be completed by early 2026, after which the study findings will be submitted for publication in peer-reviewed scientific journals. Collection of qualitative data is scheduled for the second half of 2025 and 2026.

**Conclusions:**

This study can add valuable knowledge about the effects of the violence prevention model TERMA.

## Introduction

### Background

Aggression and violence are common within forensic psychiatric inpatient care, encompassing verbal and physical threats, as well as escalations that may result in physical injuries [1,2]. A meta-analysis found that 17% of patients in psychiatric inpatient care had been involved in at least one incident of interpersonal violence [3], and research indicates that the proportion is even higher, exceeding 20%, in forensic psychiatric inpatient care [4]. Studies from forensic psychiatric care report a higher prevalence of patients who are violent compared to acute care settings and general psychiatric hospitals [5]. Several factors could contribute to the escalation of aggressive incidences in forensic psychiatric inpatient care, including shortage of staff; insufficient knowledge or practice in aggression management; and changes in patient demographics, prevalence of mental health disorders, treatment approaches, and institutional policies [5].

In psychiatric (inpatient) care, aggression and violence have traditionally been seen as linked to mental illness and other individual patient characteristics. Therefore, response has centered on reactivity and control, and staff education has emphasized self-defense, control, and restraint techniques. However, over the last 2 decades, focus has shifted toward seeing aggressive patient behavior as a result of a complex interplay of diverse internal, external, and situational factors. Violent behavior may lead to injury but may also have other consequences, such as diminished therapeutic relationships [6], lower job satisfaction, and increased psychological stress [7,8]. Previous research on staff and patient experience of aggression and violence that resulted in coercive interventions (including seclusion, restraint, and medication) shows that incidents negatively affect treatment, work environment, job satisfaction, and therapeutic relationships between patients and staff [9]. Research also indicates that structured de-escalation models increase active listening between staff and patients that helped reduce seclusion and coercive methods within the ward [10]. In addition, the use of coercive measures as a response to violent behavior is problematic for both patients and staff and harmful for the therapeutic alliance. Moreover, patients experience these measures punitively [9].

To reduce the use of coercive measures, the recommended response to potential violence and aggression risk in forensic psychiatry is de-escalation of the situation [6]. It involves staff intervention before a situation reaches a point where more restrictive measures become necessary [6]. Several de-escalation models have been developed and are being used within psychiatric inpatient settings [11], including positive behavioral support [12,13], M4 (“managing the team, managing the environment, managing the patient, and managing aggression”) [14], the Bergen model [15], and the subsequent Therapeutic Meeting With Aggression (TERMA) model. A common objective among these models is the reduction of coercive interventions, but there are some distinct differences between the models [16]. Positive behavioral support focuses on bolstering staff confidence and modifying perceptions of challenging patient behavior with the primary objective of establishing a safe and secure environment [12]. It includes comprehensive staff training with a particular emphasis on enhancing communication skills and using tools to manage challenging patient behavior [12]. M4 centers on theoretical elements, including the analysis of organizational patterns of aggression, and places emphasis on risk management [14]. The Bergen and TERMA models place a central focus on treatment, communication, and the delivery of patient-centered health care within the specific context of forensic psychiatric settings. The models are designed to address and mitigate aggression and violence using a system of low-intensity interventions organized according to the patient’s aggression level, risk of violence, and history of previous violent acts [15]. At present, forensic psychiatric hospitals use a variety of de-escalation models, emphasizing both proactive and reactive measures to maintain a secure and therapeutic care environment. Communicative and cognitive de-escalation in the form of verbal discussion is one of the most common practices in de-escalation, emphasizing stimulus reduction and attempting to guide the patient away from unwanted behavior [17].

One obstacle to successful implementation of new work practices is that staff resist the change. A certain degree of resistance is common and expected when new practices are introduced [18,19]. Resistance to change refers to the reluctance or opposition displayed by staff when confronted with alterations in their work environment, practices, or procedures [20]. This resistance can manifest in various forms, such as skepticism, reluctance to adopt new practices, or active opposition to proposed changes [18,21]. Several factors contribute to resistance to change, including uncertainty and fear of the unknown, comfort with the status quo, lack of involvement in the change process, concerns about competence, previous negative experiences, workload and time constraints, and current cultural and organizational factors [22]. A number of factors are important to induce staff receptiveness to change, including work atmosphere, an effective framework of well-established procedures and methods, visible support for the change from leadership [18], transparent and open communication about the reasons for the change, the expected benefits, and how it aligns with broader organizational goals [22], and regular updates and opportunities for staff to ask questions or express concerns [18]. This significantly contributes to creating a sense of security and comfort, potentially resulting in a reluctance to embrace change or explore new techniques and work methodologies among experienced staff [21]. In addition, staff needs the necessary resources, tools, and technology to implement and sustain the changes effectively [18].

In Sweden, someone having been found guilty of a crime committed under the influence of a severe mental disorder can be sentenced to forensic psychiatric care instead of prison. Forensic psychiatric care is compulsory, and the sanction is not determined by time, as stipulated by the Swedish Courts’ Forensic Mental Health Act. Recent measurements indicate that the median care duration is 7.5 years but can be even longer [23]. Patients within forensic psychiatric care in Sweden represent a highly heterogeneous group [24]. Most common diagnoses include different forms of psychotic disorders, substance use disorders, and personality disorders. Comorbidity is prevalent, and 2 or 3 concurrent diagnoses are very common [25]. A large proportion of patients in forensic psychiatry are offenders who have committed violent crimes, and consequently, they present a distinctive set of challenges related to aggression and violence [24,26].

Delivering health care services within the framework of mandatory care poses challenges, including amotivation, noncompliance, and impediments to trust between patients and staff [27]. The indefinite duration of care adds complexity to the task of establishing a secure health care environment [23]. Forensic psychiatric inpatient care confronts these challenges and requires adaptation to ensure the effective implementation of treatment and the resulting discharge [28]. Violence and aggression are prevalent in forensic psychiatric inpatient care [3], posing a complex challenge that requires innovative and evidence-based interventions [4,16]. Current recommendations advocate for a proactive rather than a reactive approach to dominate staff education [29].

### Objectives

There is a lack of evidence regarding the effects of de-escalation models such as the TERMA model. Therefore, the aim of this project is to evaluate the violence prevention model TERMA regarding adverse events and perceived safety by patients and staff within forensic psychiatric inpatient care. In addition, the project will investigate whether the organizational culture influences the implementation of the TERMA model and the experiences of patients and staff in situations involving threats, violence, and the use of coercive measures. The project includes the following research questions:

To what extent does the implementation of TERMA impact the perceived safety and perception of violence preventative culture in the wards of staff and patients in a forensic psychiatric inpatient setting?What is the effect of implementing TERMA on the frequency of incidents of aggression and violence, health care and occupational injuries, and the use of coercive measures in a forensic psychiatric inpatient setting?How does the organizational culture of a forensic psychiatric inpatient unit impact changes in perceived safety, incidents of aggression and violence, health care and occupational injuries, and the use of coercive measures?How do patients perceive threatening and violent situations, exposure to coercive measures, and the implementation of TERMA in a forensic psychiatric inpatient setting?What are the attitudes and perceptions of staff toward working with TERMA, how do they respond to threatening and violent situations, and what is the impact of these factors on the work environment in a forensic psychiatric inpatient setting?

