## Methods

### Overview

This study uses an observational before and after design. The choice of TERMA was a pragmatic one, as it was being implemented in the clinic. However, the research design, including research questions, outcome measures, and methods of analysis, was not influenced by the clinic. The project was registered on ClinicalTrials.gov (NCT05932108) before starting the study. The protocol complies with the Standard Protocol Items: Recommendations for Interventional Trials (SPIRIT) [30,31], and the results will be reported according to established recommendations.

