These levels are designed to correspond with specific situational demands and environmental factors, optimizing their relevance and applicability. The *primary level* centers on the patient’s daily behavior and overall health status. It involves proactive measures aimed at understanding the patient’s emotional state, as well as managing stress and anxiety. Building trust and establishing balanced roles are key components at this stage. At the *secondary level*, the focus shifts to risk assessment and violence management. The aim is to cultivate mutual understanding between the patient and health care workers regarding the situation. The emphasis is on finding common ground and agreeing on acceptable solutions while preparing for further escalation if necessary.

When violence becomes inevitable, the *tertiary level* is activated. Here, the primary goal is to create a calm and secure environment for the patient, other patients, and staff. Clear leadership and low-intensity approaches are vital for diffusing tension, and physical restraint, if required, is executed with precision. Following the resolution of the situation, a situational analysis is offered to the patient to enhance understanding and prevent future incidents.

The implementation of TERMA is conducted through a staff training program consisting of 8 seminars. The seminars are divided into 4 theoretical sessions and 4 practical training sessions. The staff members first receive theoretical knowledge, followed by hands-on practice in restraint and self-defense techniques. This mixed format facilitates a holistic understanding of TERMA and equips staff with the skills necessary for implementation. The TERMA intervention will be uniformly implemented across all wards of forensic psychiatry at the Sahlgrenska University Hospital.

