### Quantitative Sources and Collection of Data

Data will be collected from questionnaires, medical records, and administrative registers. Questionnaire data will be obtained from both patients and staff at baseline and 6- and 12-month follow-up. To assess perceived safety, data will be gathered from both patients and staff members using the E13 [15]. The E13 assesses self-reported safety, feelings of security, and violence preventative culture within the hospital wards. Respondents will be presented with 13 statements, and their level of agreement will be rated on a 4-point Likert scale, ranging from (1) “completely disagree” to (4) “completely agree,” with an additional “do not know” option available [15]. The questionnaire assigns a value of “1” to response options 3 and 4 for all items, except for the 3 negative items (items 4, 8, and 12), where a value of “1” is assigned to options 1 or 2 [15]. All other responses are scored as “0.” Thus, the sum score range for each questionnaire was 0‐13 [15].

The OVQ will be used to investigate the organizational culture in the wards. The survey will only be distributed to staff. The OVQ is based on the concepts of the competing value framework, which measures the 4 dimensions within each business: collaboration, creation, competition, and control [20]. These values compete in a very real sense for a business’s limited resources (funding, time, and people). The questionnaire contains 52 items, each rated on a 10-point Likert scale from “disagree” to “strongly agree” [20]. Data regarding incidents of threats and violence, patient and occupational injuries, and the application of coercive measures will be extracted from medical records and the local clinical registry known as MedControl PRO. These data points will be collected in 3 distinct phases: before the introduction of TERMA, at the 6-month juncture following implementation, and upon the culmination of a 12-month period. For staff members, supplementary descriptive data will be collected through a dedicated questionnaire, while background information pertaining to patients will be retrieved from their medical records.

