### Outcomes

The primary outcome will be change in perceived safety reported by both patients and staff, as measured by the E13 scale total score (0‐13), between baseline and 6- and 12-month follow-up assessments. Secondary outcomes include changes in organizational culture, as measured by the OVQ and its subscales between baseline and 6- and 12-month follow-up assessments. Correlation between E13 and OVQ scores at baseline, 6-month follow-up, and 12-month follow-up will be analyzed. The number and severity of aggression incidents from 1 year before baseline to 1 year after conclusion of the study will be analyzed.

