## Results 

Recruitment of participants began in July 2023 and concluded by the end of 2024. Collection of data from patient and staff questionnaires will be completed 13 months thereafter. Data from administrative registries will be collected retrospectively for the entire period. Data collection and analysis of quantitative data are expected to be completed by early 2026. Collection of data for the qualitative studies is planned for the second half of 2025 and 2026, and analysis is planned for 2026 and 2027. Results from this project will be published in peer-reviewed scientific journals and presented at international conferences.

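### Research questions 1 and 2 and the Discussion promise the effect of TERMA, but an uncontrolled before/after comparison can only show change after its implementation

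*Protocol article*

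**What the plan says.** **The questions.** In the Objectives section, research question 1 asks "To what extent does the implementation of TERMA impact the perceived safety and perception of violence preventative culture" among staff and patients. Research question 2 asks "What is the effect of implementing TERMA on the frequency of incidents of aggression and violence", and extends this to injuries and coercive measures. The abstract's Conclusions state: "This study can add valuable knowledge about the effects of the violence prevention model TERMA". The Discussion describes the project as assessing effectiveness and as giving insight into TERMA's impact on perceived safety.

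**The design.** The Methods overview is open about it: "This study uses an observational before and after design". The setting is one forensic psychiatric clinic. On exposure, the section on design and implementation of TERMA says: "The TERMA intervention will be uniformly implemented across all wards of forensic psychiatry" at that hospital.

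**The measurements and test.** "Questionnaire data will be obtained from both patients and staff at baseline and 6- and 12-month follow-up". Under Outcomes, "The primary outcome will be change in perceived safety reported by both patients and staff", measured by the E13 total score (0 to 13). Under Statistical Analysis, changes are tested with a paired t test or the Wilcoxon signed-rank test, with significance at P<.05. The regression models named there concern organizational culture, not time.

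**The calendar.** "Recruitment of participants began in July 2023 and concluded by the end of 2024"; the Results section adds that questionnaire collection ends 13 months later.

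**The concern.** The questions are causal and the stated analysis is not. A paired before/after test has *no change* as its null hypothesis. Rejecting it says that the mean score moved; it does not say why.

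The article itself names rival explanations. Its Background lists staff shortage, patient demographics, treatment approaches and institutional policies as contributors to aggression, and the Discussion calls staff shortage a prominent factor. All of these can shift between July 2023 and early 2026. With every ward exposed there is no untreated ward to compare with, and one E13 baseline per respondent gives no individual pre-implementation trend. The Discussion text at hand states no limit on attributing change to TERMA.

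At stake is what the study can be said to have found. A clinic deciding whether to adopt TERMA could take a significant paired test, reported as the answer to a question about effect, as evidence of effectiveness.

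**Working it through.** The article states no sample size, power, SD or effect size, so there is no figure of its own to reproduce. The calculation below only illustrates how much the distinction can matter.

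**Inputs from the article**
- Two-sided test at 0.05 on paired change (Statistical Analysis).
- 84 rehabilitation rooms, some shared, and about 290 staff (Participants and Setting). These are rough upper guides to the number of patient and staff pairs; consent and drop-out will lower them.

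**Assumptions, not in the article**
- True TERMA effect of zero.
- A common drift d, in units of the SD of the paired change: 0.2 or 0.3.
- Pair numbers n of 35, 60 and 150.

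**Formula (normal approximation)**

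P(significant) = Φ(d√n − 1.96) + Φ(−d√n − 1.96)

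**Drift 0.2 SD**
- n = 35: d√n = 0.2 × 5.916 = 1.183; Φ(−0.777) + Φ(−3.143) ≈ 0.22
- n = 60: d√n = 0.2 × 7.746 = 1.549; Φ(−0.411) + Φ(−3.509) ≈ 0.34
- n = 150: d√n = 0.2 × 12.247 = 2.449; Φ(0.489) ≈ 0.69

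**Drift 0.3 SD**
- The same steps give about 43%, 64% and 96%.

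**Check with the noncentral t distribution at the room and staff counts**

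| Drift (SD of change) | n = 84 | n = 290 |
|---|---|---|
| 0.1 | 14.8% | 39.7% |
| 0.2 | 44.1% | 92.4% |
| 0.3 | 77.6% | 99.9% |

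Drift gives an 80% chance of P<.05 at about 0.31 SD with n = 84 and about 0.17 SD with n = 290. With no drift the rate is 5%.

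**What a comparison group would have done.** In 20,000 simulated studies with a 0.3 SD drift and no TERMA effect, a two-sample test of change against a hypothetical concurrent control with the same drift rejected in 4.8% (total n = 84) and 4.9% (total n = 290). The before/after test rejected in 77.8% and 99.97% of the same studies. The excess comes from the missing comparison, not from a fault in the test.

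**The case against.** The strongest reply is that nothing is hidden. The article calls the study observational and before/after throughout, and it explains that TERMA was already being introduced in the clinic, so a control ward was not on offer. The Outcomes and Statistical Analysis sections already speak neutrally of change between measurements. Interviews with patients and staff, and incident data from one year before baseline, add further evidence. All of this is fair, and the design is not itself the fault. But the neutral wording does not reach the research questions or the Discussion, which still promise an effect.

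Three stronger readings are tempting and are not supported:

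- *That any drift would be declared an effect.* No passage equates P<.05 with TERMA being effective; the article says only that such values are statistically significant. Only drift large enough to reach P<.05 would be flagged, and adverse drift could hide a real benefit.
- *That the paired test has an inflated error rate.* Under drift the scores really do change, so rejecting no change is correct. The mistake would lie in the causal reading.
- *That the lack of a calendar-time or trend model is an omission.* Such a model commonly belongs in a full protocol or analysis plan, neither of which is shown. For E13 it would also need ward training dates that differ between wards. The article gives none and describes uniform implementation.

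**Conclusion.** The concern holds as a mismatch between question and analysis. Research questions 1 and 2 and the Discussion ask for an impact, effect or effectiveness that the stated primary E13 analysis cannot identify. The text at hand sets no limit on attribution.

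The percentages show the scale of the problem under assumed drift and pair numbers; they are not a forecast for this study, and no passage reports that drift occurred. The conclusion does not depend on them. It follows from the absence of a comparison group, the exposure of all wards, the single E13 baseline and the paired test. For research question 2, the year of incident data before baseline could support a trend-adjusted analysis, but the article does not state one, so the wording point applies there too. The data remain useful for describing what changed.

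**What to change.** 1. Reword research questions 1 and 2, and the conclusions, as *change after implementation of TERMA*. Bring the effectiveness and impact wording in the Discussion into line.
2. State in advance that a significant before/after change will not by itself be reported as an effect of TERMA, because changes in staffing, patient mix or policy over 2023 to 2026 cannot be separated from it.

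This needs no new data. The cost is a weaker claim. Recruitment has closed, so a concurrent control among new enrolees is no longer available; the interpretation can be fixed before the results are reported.

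A calendar-time sensitivity model for E13 should be considered only if ward training dates were recorded and differ between wards. If all wards were trained together, calendar time and time since training cannot be separated. Feasibility and precision cannot be judged from the article, so no standard error is offered.
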